### Ethical considerations

This pilot study and its protocols have been approved by the Korean Public IRB and the National Cancer Center IRB (IRB number: P01-201908-11-003; P01-202004-11-005; P01-202004-11-006; P01-202011-11-001; NCC2019-0162). The study will be conducted in compliance with the approved protocol and any deviations from the protocol will not be executed without prior review and approval from the IRB.

### Dissemination of results

The findings of this pilot study will be published in peer-reviewed scientific journals and presented at national and international conferences. The results will be published in a statistical aggregate form so that no individual information will be identifiable.

## Discussion

In this paper, we presented the objective, design, and study protocol of K-cospi. The present pilot study is planned to examine the effectiveness, complications, feasibility, and acceptability of colonoscopy as a primary method for CRC screening. FIT is provided free-of-charge as the primary CRC screening method through the NCSP in the Republic of Korea. However, their CRC screening rate was as low as 25% in 2012, and it was the lowest compared to their screening rates for other cancer types, such as stomach, liver, breast, and cervix [7]. In addition, a recent survey found that 68.7% of the participants would prefer the NCSP to adopt colonoscopy as its primary CRC screening test because it is accurate and can provide therapeutic options [6]. K-cospi was launched at an opportune time considering the low CRC screening rates of NCSP and the growing demand for colonoscopy by the national CRC screening program. Furthermore, this pilot study is of importance given that the lack of studies about the appropriateness of colonoscopy as the primary modality of CRC screening.

Previous studies have evaluated the efficacy and disadvantages of colonoscopy screening. A systematic review of observational studies of endoscopy demonstrated that the CRC incidence reduced by 69% (relative risk [RR] 0.31; 95% confidence interval [CI] 0.12–0.77) and mortality reduced by 68% (RR 0.32; 95% CI 0.23–0.43) [8]. Elmunzer et al. [9] found that colonoscopy was more effective than guaiac fecal occult blood test (gFOBT) (RR 0.49; 95% CI 0.30–0.76) in reducing CRC mortality. In addition, the detection rates for advanced adenoma with colonoscopy was significantly higher than those with gFOBT or FIT [10, 11]. However, the mortality rate within 30 days after endoscopy, major bleeding rate, and perforation rate were estimated to be about 1 in 15,000, 0.8 in 1,000, and 0.07–0.4 in 1000 procedures, respectively [12–15]. In other words, colonoscopy is vastly effective in screening for CRC but is highly risky at the same time. Therefore, it is important to evaluate the benefits of colonoscopy screening against its disadvantages in terms of efficacy, process, and cost. Cost is a decisive criterion for the implementation of a screening intervention [16].

Currently, there are four on-going large-scale randomized controlled trials that compare colonoscopy with no screening or fecal immunochemical testing for CRC incidence or mortality in 10–15 years [17]. The trials were launched between 2009 and 2014, and the results of these trials will presumably be presented in 10 years. Therefore, findings from the present pilot study regarding the suitability of colonoscopy as the primary method for CRC screening in organized population-based screening programs are necessary to provide critical insights into the future direction of national CRC screening program in the Republic of Korea.

The protocol of this pilot study has some limitations that should be noted. First, we will not randomizing participants into the two study arms. It is difficult to carry out a randomized controlled trial because FIT is provided free-of-charge every year through the Korean NCSP. To overcome this shortcoming in the study design, the participants will be matched according to their gender and age with the data from the Korean NCSP for CRC to compare the performances of FIT and colonoscopy. Second, the generalizability of the study findings will be limited because the participation rate in this pilot study, the characteristics of participants, and the clinical setting of medical institutions may vary depending on regional characteristics. To minimize this limitation, we selected pilot sites that represent the CRC epidemiology of the whole country and have a balanced characteristic of urban and rural areas. In addition, we evenly included first, second, and tertiary hospitals so that the study can be conducted under real-world circumstances.

In summary, the findings of this pilot study will provide critical information regarding the acceptability and feasibility of colonoscopy as the primary modality of the Korean National Cancer Screening Program. They will lead to more effective and efficient screening programs for CRC.

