## Background

Colorectal cancer (CRC) was responsible for more than 10% of the global cancer burden in 2018 [1]. It is the third most common cancer in men and the second most common cancer in women worldwide, with more than 730,000 new cases being diagnosed each year [2]. CRC has a high burden of disease in Korea as well as the second most common cancer and the third most common cause of cancer-related deaths in men and women combined [3].

CRC starts as a locally confined polypoid precursor lesion and has a long preclinical stage, with most symptoms presented at an advanced stage. Morbidity and mortality of CRC can be significantly reduced if the disease is diagnosed and treated at an earlier stage [4, 5]. Therefore, screening for CRC before the development of symptoms may be beneficial for improved long-term outcomes. There are several screening modalities for CRC, which include fecal occult blood test (FOBT), sigmoidoscopy, colonoscopy, computed tomography colonography, and stool or blood DNA test. Colonoscopy allows for the detection and removal of early cancer and precancerous adenoma in one-step, and thus, it may have a large effect on decreasing CRC incidence and mortality.

Since 2004 as part of the National Cancer Screening Program (NCSP), the government of the Republic of Korea has been providing annual fecal immunochemical test (FIT) for free to adults aged 50 years and older as the primary modality for detecting CRC. Individuals with a positive FIT result are then referred for either colonoscopy or double-contrast barium enema, which are both provided free-of-charge. However, 68.7% of the patients preferred colonoscopy as the primary method for CRC screening [6]. There has been consistent demand for the introduction of colonoscopy as the primary method for the national CRC screening program. However, colonoscopy is an invasive and expensive procedure. In addition, it entails a risk of complications, requires extensive bowel preparation, and is difficult to learn. Therefore, the benefits and harms of colonoscopy should be carefully evaluated. Currently, we lack population-based clinical trials investigating both the magnitude of effectiveness and the harms of colonoscopy screening for CRC.

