### Participant recruitment

Posters and leaflets have been placed in each participating medical institution, main bus and subway stops, and at public health centers within the pilot sites to raise awareness of the pilot study. In addition, the pilot study has been introduced to local newspapers of the pilot sites.

Potential participants are identified from the participating medical institutions during their visits and invited to participate if eligible. In addition, those who express interest in participating in the pilot study to the Center for K-cospia re guided to the nearest participating medical institution after eligibility screening. Table 1 lists the inclusion and exclusion criteria.

**Table 1 Tab1:** Eligibility criteria

Inclusion criteria	Exclusion criteria
Males and females aged 50–74 years	Subjects who have been diagnosed with CRC or are currently undergoing treatment for CRC
Subjects who live within the pilot sites	Subjects underwent colonoscopy screening within the last 5 years

Subjects are allowed to participate in the pilot study only once. Recruitment was initiated in August 2019 and will continue until the planned sample size is reached.

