### Data analysis plan

Colonoscopy performance, including CRC detection rate and stage-shift, will be reported during the whole study period. Participant data will be matched against the national CRC screening program database of the National Health Insurance Service to compare the performance of the colonoscopy with that of the FIT. After completion of our study, we will analyze the long-term effects of colonoscopy screening, such as CRC mortality and incidence reduction, and its cost-effectiveness by linking data with the Korean Central Cancer Registry and death certificate data of the Korean National Statistical Office. In addition, complications related to colonoscopy over the study period, and satisfaction of participants will also be described. Missing values will not be imputed. The Center for K-cospi will conduct all analyses on de-identified data.

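### The FIT comparison group is matched on gender and age only, which cannot make up for the lack of randomisation, and the article does not say that Table 1's criteria apply to it

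*Protocol article*

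**What the plan says.** The limitations paragraph of the Discussion concedes that participants are not randomised. It introduces the remedy with "To overcome this shortcoming in the study design" and continues that "the participants will be matched according to their gender and age with the data from the Korean NCSP for CRC". No third matching factor is named there. The Data analysis plan adds only the data source: "Participant data will be matched against the national CRC screening program database of the National Health Insurance Service".

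Table 1 (Participant recruitment) sets the criteria for the people who receive colonoscopy. The inclusions are "Males and females aged 50–74 years" and "Subjects who live within the pilot sites". The exclusions are "Subjects who have been diagnosed with CRC or are currently undergoing treatment for CRC" and "Subjects underwent colonoscopy screening within the last 5 years". The Background describes the programme that supplies the FIT records as "annual fecal immunochemical test (FIT) for free to adults aged 50 years and older" and mentions no exclusion for a recent colonoscopy.

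Detection of CRC is one of two primary outcomes (Outcome measures). The sample size rests on detection rates of 1.2 per 1000 with FIT and 2.2 per 1000 with colonoscopy (Sample size calculation).

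**The concern.** Matching on gender and age balances gender and age. It does nothing for recent colonoscopy, prior CRC, earlier FIT rounds, district, calendar period, or the fact that participants are clinic attenders and people who came forward. Presenting it as overcoming the absence of randomisation is therefore wrong, whatever a fuller plan may add.

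The eligibility criteria sharpen the problem. Someone with a recent screening colonoscopy has, on the evidence that the Discussion cites, a lower chance of a detectable cancer. Such people are kept out of the colonoscopy group. If they stay in the FIT denominator, the FIT rate is diluted and part of the observed difference reflects who was counted rather than which test was used. At stake is the comparison on which the sample size is built and which is meant to inform national screening policy.

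**Working it through.** **Step 1: the two groups side by side, as the article describes them.**

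| Feature | Colonoscopy participants | FIT records |
|---|---|---|
| Gender | recorded | matched |
| Age | 50–74 | aligned by the age matching |
| Residence in pilot sites | required | not mentioned |
| No prior or current CRC | required | not mentioned |
| No screening colonoscopy in 5 years | required | not mentioned |
| Calendar period | August 2019 to about December 2024 | not mentioned |
| Earlier screening | asked in the baseline questionnaire | not mentioned |

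Only the first two rows are aligned by the stated method.

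**Step 2: reproduce the plan's figure.** Alpha, power and allocation are not stated. Assume two-sided 0.05, 80% power, 1:1 and no continuity correction. With p1 = 0.0012, p2 = 0.0022 and mean 0.0017:

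n = [1.96·√(2·0.0017·0.9983) + 0.8416·√(0.0012·0.9988 + 0.0022·0.9978)]² / 0.001² = (0.114187 + 0.049029)² / 0.000001 = 26,640 per group.

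This matches the target exactly, so the arithmetic of the sample size is not in question. The planned ratio is 2.2/1.2 = 1.83.

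**Step 3: effect of a missing colonoscopy exclusion on its own.** Let f be the share of FIT attendees with a recent colonoscopy and r their detection rate relative to the others. If 1.2 per 1000 is the rate in an unrestricted FIT group (assumption), then

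eligible FIT rate = 1.2 / (1 − f + f·r).

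The article gives neither f nor r. For r, 0.31 is borrowed from the relative risk of CRC incidence in the systematic review of endoscopy cited in the Discussion. Using it as a relative detection rate is an assumption. Power is for the same two-proportion test at 26,640 per group:

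| f | Eligible FIT rate per 1000 | Ratio to 2.2 | Power | n per group for 80% |
|---|---|---|---|---|
| 10% | 1.2/0.931 = 1.29 | 1.71 | 71% | 32,933 |
| 20% | 1.2/0.862 = 1.39 | 1.58 | 60% | 43,119 |
| 30% | 1.2/0.793 = 1.51 | 1.45 | 45% | 61,679 |

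At f = 20%, varying r from 0.2 to 0.5 gives ratios of 1.54 to 1.65 and power of 55% to 66%. With r = 0.77, the upper confidence limit of the cited relative risk, the eligible rate is 1.2/0.954 = 1.26 and power is about 75%.

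**Step 4: effect of a missing prior-CRC exclusion.** Now suppose that the true eligible FIT rate is 1.20, with f = 20% and r = 0.31. Add a 0.5% share of attendees with prior CRC, of whom a fraction q is counted as screen-detected (all assumptions). The rate in the unrestricted group is

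0.995·1.2·0.862 + 0.005·1000·q = 1.029 + 5q per 1000.

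- q = 2%: 1.029 + 0.10 = 1.13, below 1.20, so the net bias still favours colonoscopy.
- q = 5%: 1.029 + 0.25 = 1.28, above 1.20, so the net bias reverses.
- Break-even: q = (1.20 − 1.029)/5 = 3.4%.

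The sign therefore depends on quantities that the article does not give.

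**Step 5: effect of the matching ratio.** No 1:1 ratio is stated, and the comparator is a national database. The power formula, with pooled p̄, is

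Φ{[(p2 − p1) − 1.96·√(p̄(1 − p̄)(1/n1 + 1/n2))] / √(p1(1 − p1)/n1 + p2(1 − p2)/n2)}.

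With n2 = 26,640 and five FIT records per participant (n1 = 133,200), the three rows of Step 3 give power of about 91%, 83% and 70%. More comparators restore power. They do not remove the bias in the ratio.

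**The case against.** The strongest reply is that choosing matching variables and restricting the pool are separate steps, and the Discussion describes only the first. This is a condensed article. Restriction of the FIT records, the index period, removal of participants from the pool and covariate adjustment could all stand in the full protocol or analysis plan. That reply holds against one tempting inference, namely that the FIT group is definitely built without the eligibility criteria. No section says that they are applied, and none says that they are not.

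A reader might also infer that the comparison is biased towards colonoscopy. Only the colonoscopy exclusion has a clear direction. Step 4 shows that prior-CRC records could offset or reverse it, and district, calendar period and earlier FIT have no stated direction. Nor can a given fraction of the planned difference be called an artefact. The article does not say which population the 1.2 or the 2.2 per 1000 describes, and the power figures depend on an assumed 1:1 ratio.

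What remains is what the text does state: a method with two named factors, offered as the cure for non-randomisation. That is a described choice rather than an omitted detail, and it is inadequate for the purpose given.

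**Conclusion.** The point stands in a conditional form. Gender and age matching cannot overcome the lack of randomisation, and the text should not say that it does. The CRC, 5-year colonoscopy and residence criteria are stated for colonoscopy participants only. If they are not carried over to the FIT records, the primary detection-rate comparison is confounded. The missing colonoscopy exclusion taken alone would favour colonoscopy. The net direction and size cannot be determined from the article.

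The Step 3 ratios and power show the order of magnitude that is possible. They are not estimates, because they rest on an assumed f, a borrowed r, an assumed unrestricted population for the 1.2 per 1000 rate and an assumed 26,640 FIT comparators. An unknown direction is itself a reason to align the groups before the comparison is run.

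**What to change.** - **Comparator definition.** State that FIT comparators are national-programme attendees over the same calendar period who meet the Table 1 criteria at their index FIT: age 50–74, resident in the pilot sites, no prior CRC and no colonoscopy within 5 years. K-cospi participants are excluded from the pool.
- **Same definition of recent colonoscopy in both groups.** Table 1 refers to screening colonoscopy. Removing comparators with a colonoscopy for any reason would create a new asymmetry. Participants' history comes from a questionnaire and comparators' would come from linked records, so the definitions should agree as far as those records allow, and any remaining gap should be stated.
- **Matching or adjustment.** Use sex, age, district, calendar period and earlier FIT participation. Keep the sex-and-age-only match as a sensitivity analysis.
- **Wording.** Replace *overcome* with *partly reduce*, and list residual confounding from volunteer selection as a limitation.

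The cost is a somewhat larger data request and a smaller FIT pool. Linkage to the screening database is already planned, but whether its records capture all screening colonoscopies is not stated and should be checked first. Recruitment and participant procedures do not change.

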### Trial status

Protocol version 2.5 as of November26, 2020The date recruitment began: August 8, 2019Approximate date when recruitment will be completed: December 31, 2024

## Data Availability

The datasets used/analyzed in this study are available from the corresponding author on reasonable request.

## Abbreviations

CRC: Colorectal cancer
FOBT: Fecal occult blood test
NCSP: National Cancer Screening Program
FIT: Fecal immunochemical test
PEG: Polyethylene glycol
IRB: Institutional review board
gFOBT: Guaiac fecal occult blood test
RR: Relative risk
CI: Confidence interval
